#### Safety and adverse events monitoring

2.8.5

1.Physical examination will be conducted and vital signs will be collected at every visit after randomization. The results of the physical examination and vital signs will be reviewed to determine the normality and abnormality of each examination.2.Patient Reported Outcome-Common Terminology Criteria for Adverse Events (PRO-CTCAE)CTCAE evaluated by the medical staff involves assessment of symptoms by the clinician, and this may lead to the omitting or underestimation of side effects experienced by the patients. Therefore, the importance of patients directly explaining their overall health status is increasingly emphasized. In this study, the PRO-CTCAE^[22]^ questionnaire will be used to assess patient safety. It is expected that the main side effect of neuropathic pain treatment will be aggravation of pain. Thus, terms of pain-related symptoms in the PRO-CTCAE will be selected and used to construct a questionnaire. The assessment will be conducted at 2, 4, and 8 weeks.3. Evaluation of objective and subjective symptoms as well as adverse reactions will be conducted at every visit after randomization.-The investigator must record all adverse reactions and concomitant medications used during the clinical trial.-Adverse reactions and concomitant medications will be recorded in the case record form. For adverse reactions, the symptoms, signs, duration (start date/end date), severity, outcome, seriousness, causal relationship with the intervention, and actions taken for the reaction will be recorded.-Symptoms or signs that are present before participation in the study will not be recorded as adverse reactions. However, changes in the frequency, severity, and scope of the symptoms after participation in the study will be recorded as adverse reactions.-Additionally, the name of ingredients, dosage, administration period, and reasons for administration of concomitant medications will be recorded in detail.

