# Exploratory evaluation is not conduced for patients who have completed treatment early. For patients who dropped out of the study, exploratory evaluation is conducted after 4 weeks from dropping out (exploratory effectiveness evaluation for dropout participants can be conducted through telephone counseling instead of in-person visits).

∗∗ Evaluation of direct non-healthcare, direct non-healthcare, and lost productivity costs.

†† Those patients who reported adverse reactions will complete EQ-5D by recalling time of adverse events.

Patients who undergo 1 NBT and show continued symptoms (patient's subjective pain improvement is less than 50% after the procedure or the numeric rating scale (NRS) score being 5 or higher) will undergo screening at 1 week after the first procedure. For screening, demographic information, medical history, physical examination, vital signs, questionnaire survey, laboratory test, and selection/exclusion criteria will be evaluated. Randomization and group allocation will be performed at screening and baseline. Fifty patients will be enrolled and randomly divided into 2 groups. Patients who are judged suitable for the study after the screening test and voluntarily agree to participate will be randomly assigned to either the NBT single treatment group (usual care group) or NBT + deeply inserted acupotomy treatment group in a 1:1 ratio (Fig. 1). Thereafter, the randomly assigned patients will undergo primary and secondary outcome evaluations and economic evaluation.

The NBT + deeply inserted acupotomy group will receive 8 acupotomy treatments (at visits 2, 3, 5, 6, 7, 8, 10, and 11) for 4 weeks as well as additional 2 NBTs (at visits 4 and 9) for 4 weeks. Then, the group will be followed-up for 4 weeks after the intervention treatment. The standard care group will undergo two NBTs (at visits 2 and 4) for 4 weeks and will be followed-up for 4 weeks after the intervention treatment. Primary and secondary outcomes, economic evaluation, and assessment of drug administration history will be conducted at visits 1, 6, and 11, and at the end of follow-up. To evaluate safety, evaluation of adverse events, vital signs, and economic feasibility will be conducted at every visit from visit 2 to visit 12. Laboratory tests will be conducted only at screening.

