#### Inclusion criteria

2.5.1

The inclusion criteria are as follows:

1.adult men and women aged 18 to 85 years;2.patients diagnosed with spondylosis with lumbosacral disc disorder (injury), spinal stenosis, or lumbosacral radiculopathy through radiological examination (magnetic resonance imaging or computed tomography) within 6 months prior to participation in the clinical trial (in case of patients suspected of lumbosacral radiculopathy but with no imaging records at the time of screening test, magnetic resonance imaging or computed tomography scans will be performed to check whether they meet the diagnostic criteria);3.patients with symptoms related to lumbosacral radiculopathy, such as radiological pain, muscle weakness, and paresthesia of the lower extremities or those diagnosed with radiculopathy of the lumbosacral spine through a physical examination;4.patients who will undergo NBT within 2 weeks after the start of the clinical trial, and patients whose subjective pain improvement will be less than 50% after the procedure or the NRS score will be 5 or higher;5.patients who can read, understand, and answer the symptom questionnaire; and6.patients who volunteer to participate and give their written consent while agreeing to the clinical trial plan and follow-up.

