#### Secondary outcome

2.8.2

1.NRSThe patient selects a number that corresponds to the pain level^[17]^ (NRS-11 that evaluates pain from a score of 0–10 will be used). In this study, changes in pain level will be assessed at 0 (screening test), 2, 4, and 8 weeks and compared with that before study participation. Low back pain and lower extremity pain will be separately evaluated.2.European Quality of Life 5 Dimension (EQ-5D)Changes in quality of life will be assessed at 0 (screening test), 2, 4, and 8 weeks and compared with that before study participation. EQ-5D evaluates 5 domains: mobility, self-care, usual activity, pain/disability, and anxiety/depression. It is widely used to assess quality of life.^[18]^
3.McGill Pain Questionnaire (MPQ)The Korean version of MPQ^[19]^ will be used to assess changes in pain at 0 (screening test), 2, 4, and 8 weeks and compared with that before study participation.4.Korean version of Roland–Morris Disability Questionnaire (RMDQ)The Korean version of RMDQ^[20]^ will be used to assess changes in pain at 0 (screening test), 2, 4, and 8 weeks compared with that before study participation.

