**3. Safety assessment**

Descriptive statistics will be conducted to analyze PRO-CTCAE questionnaire items, number of adverse events, number of patients with adverse events, severity of events, and causal relationship of adverse events with the intervention for each dose group. Nonparametric methods may be used if necessary.

Vital signs, physical examination results, and subjective complains of patients will be comprehensively reviewed to perform statistical analysis on items that are considered clinically significant by the researcher. Continuous variables will be presented using the number of observations, mean, standard deviation, median, and minimum/maximum values, and differences in the mean between the 2 groups will be analyzed using paired *t*-test or Wilcoxon's signed rank test. Chi-Squared test or Fisher Exact test will be conducted for analysis of adverse events. Moreover, clinically significant changes will be compared between groups through generalized estimating equation analysis to assess statistical significance.

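### The PRO-CTCAE pain items, chosen to detect aggravation of pain, have no pre-treatment value, so worsening from entry on those items cannot be determined

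*Protocol article*

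**What the plan says.** Safety and adverse events monitoring (2.8.5) explains that clinician-rated CTCAE is not enough because "this may lead to the omitting or underestimation of side effects experienced by the patients". It then names the harm of interest: "It is expected that the main side effect of neuropathic pain treatment will be aggravation of pain". From this it follows that "terms of pain-related symptoms in the PRO-CTCAE will be selected and used to construct a questionnaire". The schedule is stated outright: "The assessment will be conducted at 2, 4, and 8 weeks".

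The Inclusion criteria (2.5.1) admit "patients whose subjective pain improvement will be less than 50% after the procedure or the NRS score will be 5 or higher", so the trial selects for pain that has outlasted a first nerve block.

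For the NRS, the Secondary outcome section (2.8.2) plans that "changes in pain level will be assessed at 0 (screening test), 2, 4, and 8 weeks and compared with that before study participation". The EQ-5D, MPQ and RMDQ follow the same four time points there, as do the ODI in 2.8.1 and the productivity questionnaire in 2.8.6.

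For analysis, the Safety assessment item of the Statistical analysis section says "Descriptive statistics will be conducted to analyze PRO-CTCAE questionnaire items" and mentions no change from entry.

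**The concern.** Aggravation is a change from an earlier state. An instrument chosen to show it needs a value from before treatment, above all in patients who enter with the symptom already present. A raised pain item at week 2 may be the radicular pain that made the patient eligible, or pain brought on by treatment, and the item alone cannot say which.

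This is not a detail left to an analysis plan. The assessment times are stated, and a value not collected before treatment cannot be recovered by later analysis. Safety is part of the trial's stated objective, and the protocol introduces this questionnaire to cover a weakness it sees in clinician reporting.

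**Working it through.** **1. Schedules side by side.**

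| Measure | Section | Weeks |
|---|---|---|
| ODI | 2.8.1 | 0, 2, 4, 8 |
| NRS (back, leg), EQ-5D, MPQ, RMDQ | 2.8.2 | 0, 2, 4, 8 |
| Productivity questionnaire | 2.8.6 | 0, 2, 4, 8 |
| PRO-CTCAE pain items | 2.8.5 | 2, 4, 8 |

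Week 0 is written out for the other repeated scales, so its absence for the PRO-CTCAE reads as the schedule itself and not as shorthand. Table 1 names the PRO-CTCAE in no row or footnote, and its adverse reaction row begins at visit 2.

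**2. Can week 2 serve as a baseline?** Table 1 places the week-2 evaluation at visit 6 of the combination arm (days 12–14). Before that visit the combination arm has acupotomy at visits 2, 3 and 5 and a nerve block at visit 4 (days 7–8). The control arm has its first trial nerve block on the same days 7–8. Both arms have been treated, and differently, so week 2 is not a baseline.

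**3. What can still be estimated on these items.**
- Change from week 0: not available for any patient.
- Change from week 2 to weeks 4 and 8: available. Five of the eight acupotomy sessions (visits 6, 7, 8, 10 and 11) and the second nerve block fall at or after the week-2 visit.
- Difference in item levels between arms at weeks 2, 4 and 8: available, and unbiased in expectation through randomisation.

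**4. Sample size and chance imbalance.** The protocol's figure reproduces: 20/(1 − 0.20) = 25 per arm, 50 in total. With 20 evaluable per arm, the standard error of a baseline difference between arms is SD × √(2/20) = 0.316 SD. A 95% range for chance imbalance is therefore about ±1.96 × 0.316 = ±0.62 SD. If entry and follow-up scores correlate at r, an imbalance at that limit carries r × 0.62 SD into the follow-up comparison: 0.25 SD at r = 0.4 and 0.37 SD at r = 0.6. Without entry scores this can be neither seen nor adjusted for on these items. The values of r are assumptions.

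**5. Precision.** Residual variance after baseline adjustment is 1 − r²: 0.84, 0.75 and 0.64 for r = 0.4, 0.5 and 0.6. These correlations are not in the protocol either, and the gain applies only to an adjusted comparison of means, whereas the plan for these items is descriptive.

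**6. Illustration of what a high score would mean.** A simulation assumed a 0–4 item cut from a latent 0–10 pain score at 1, 3, 5.5 and 8; entry mean 6 (SD 1.5); week-2 mean 4.5 or 5.5 (SD 2); and correlation 0.3 to 0.7. Of patients scoring 3 or 4 at week 2, about 13% to 41% were worse than at entry. All of these inputs are assumed. The result shows only that, under such conditions, a high score would mostly reflect pain already present.

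**The case against.** A reader might infer that the trial cannot detect aggravation of pain. The documents do not support that. Back and leg pain are scored separately on the NRS at week 0 and at each follow-up, the MPQ has the same schedule, and both are patient-reported, so they do not share the weakness attributed to clinician rating. This stands. They remain efficacy outcomes on other scales, however. The protocol defines response on the NRS but gives no rule for worsening, and neither scale can supply a change score on a PRO-CTCAE item.

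A reader might also infer that the protocol's rule on pre-existing symptoms (recorded as adverse reactions only if they change) cannot be applied. It can. That rule governs what the investigator records, and visit 1 supplies history, examination, NRS, MPQ, ODI and RMDQ for it.

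Nor is the PRO-CTCAE the only safety measure taken in both arms at the same times. Adverse reaction monitoring, vital signs and physical examination are ticked at the shared visits at weeks 2, 4 and 8 and at both nerve block visits.

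Finally, the selected pain terms are not listed, so how far they overlap with entry radicular pain is inferred from the eligibility criteria and not shown. The missing Table 1 entry is weak evidence alone, since an article condenses and the timing is given in the text. Both points are fair. They limit the size of the finding but leave the stated schedule as it is.

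**Conclusion.** The point holds in a limited form. As scheduled, the PRO-CTCAE pain items cannot show worsening from entry in any patient, and their between-arm comparison cannot be adjusted for entry pain or checked for imbalance. That is a real mismatch between the reason given for choosing the items and the times at which they are taken.

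It would go too far to say that the questionnaire is uninformative or that worsening pain goes unmeasured: levels can be compared without bias between arms, change after week 2 is measurable, and the NRS, MPQ and adverse reaction records remain. The primary ODI analysis and the sample size are unaffected.

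The loss of change from entry rests only on the stated schedule and Table 1. The figures for imbalance carry-over, precision and the share truly worse depend on correlations and distributions that the protocol does not give.

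**What to change.** Give the same PRO-CTCAE items at visit 1, before randomisation, so that the schedule becomes 0, 2, 4 and 8 weeks like the other patient-reported scales. Add the questionnaire to Table 1. In the Safety assessment item of the Statistical analysis section, state that worsening from baseline on each item and baseline-adjusted scores will be reported by arm, alongside the descriptive statistics already planned.

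The cost is a few extra questions at a visit where patients already complete several questionnaires. No change to sample size, significance level or primary analysis is needed. The change has to be made before patients are treated, because the entry value cannot be collected afterwards.

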#### Evaluation of economic feasibility

2.8.6

1.Demographic characteristicsMarital status, occupation, education level, religion, household income, etc., will be recorded by the patients at the first visit.2.EffectivenessEQ-5D will be recorded by the patients at 0, 2, 4, and 8 weeks.3.Safety:EQ-5D: Patients who reported adverse reactions at all visits after randomization will self-report the time of adverse events through memory recall.4.CostDirect medical cost will be asked by the investigator at 0, 2, 4, and 8 weeks, and the patients will report in the CRF.-Cost of deeply inserted acupotomy: data on institutional cost-Expenses related to inpatient, outpatient, and emergency room treatment when visiting a medical institution for lumbosacral radiculopathy-Expenses for rescue/concomitant medications-Expenses for other instruments, treatment materials, and home remediesDirect nonmedical cost will be asked by the investigator at 0, 2, 4, and 8 weeks, and the patients will report in the CRF.-Transportation fee-Nurse fee-Patient time expenditure costProductivity loss cost: the patients will self-complete the iMTA Productivity Cost Questionnaire at 0, 2, 4, and 8 weeks-iMTA Productivity Cost Questionnaire

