**4. Economic feasibility evaluation**

Economic feasibility will be evaluated on patients who participated in the clinical trial at least once since visit 2. The economic endpoint to assess cost-effectiveness will be incremental cost-utility ratio, which will be calculated based on the difference in cost and quality-adjusted life year between the experimental and control groups. Quality-adjusted life year will be calculated using EQ-5D measured at the time of visit.

$$\text{ICUR}=\frac{\text{Total Cost}\;(\text{treatment group})-\text{Total Cost}\;(\text{control group})}{\text{Quality-adjusted life year}\;(\text{treatment group})-\text{Quality-adjusted life year}\;(\text{control group})}$$

A. Time horizon

Basic time horizon for analysis will be 4 or 8 weeks. If long-term follow-up beyond 8 weeks is required, the Markov model will be used. Transition probabilities will be estimated based on clinical data collected over 8 weeks. In addition, if the time horizon exceeds 12 months, the unit of cost will be in Korean currency unit (won) for specific years, and a discount rate of 4.5% will be applied based on the economic feasibility evaluation guidelines of the Health Insurance Review and Assessment Service.

B. Analysis perspective

Societal perspective and restricted societal perspectives will be applied to include direct nonhealthcare, direct nonhealthcare, and lost productivity costs.

C. Sensitivity analysis

Deterministic sensitivity analysis will be conducted on all possible parameters and a tornado diagram will be presented. Probabilistic sensitivity analysis will be conducted using the distribution and representative values of all possible parameters. In addition, bootstrap using individual patient level data will be conducted to present the distribution of the economic feasibility evaluation effect index and 95% confidence intervals.

D. Assumptions for missing values

Last-Observation-Carried-Forward analysis method, a conservative method of underestimating missing values in cases where the result is expected to improve over time within the time horizon, is widely used to correct for missing values in clinical studies. Herein, the Last-Observation-Carried-Forward method will be used to assume missing values. In other words, if the patient is withdrawn from the study or completes treatment early, the last measured values will be used for all remaining visits to conduct analysis.

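### The cost list counts facility care only for radiculopathy visits, so care for a non-pain complication of a trial procedure falls outside total cost, contrary to the stated societal perspective

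*Protocol article*

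**What the plan says.** Section 2.8.6 lists the costs to be collected at 0, 2, 4 and 8 weeks. The only line for care at a medical institution, apart from the acupotomy itself, is "Expenses related to inpatient, outpatient, and emergency room treatment when visiting a medical institution for lumbosacral radiculopathy". Other lines carry no such limit: "Expenses for rescue/concomitant medications", other treatment materials and home remedies, transport, nursing, patient time, and productivity loss by the iMTA questionnaire. Direct medical costs are obtained by asking the patient.

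In section 2.9, part 4, "The economic endpoint to assess cost-effectiveness will be incremental cost-utility ratio", the difference in total cost divided by the difference in QALYs. "Societal perspective and restricted societal perspectives will be applied", and "Basic time horizon for analysis will be 4 or 8 weeks". On the effect side, "Quality-adjusted life year will be calculated using EQ-5D measured at the time of visit".

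Table 1 also has a row for the safety part of the economic evaluation at every visit after baseline. Its footnote says: "Those patients who reported adverse reactions will complete EQ-5D by recalling time of adverse events". Section 2.8.6 repeats this item under safety. Section 2.8.5 requires that "The investigator must record all adverse reactions and concomitant medications used during the clinical trial", with start and end dates and causal relationship for each reaction.

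**The concern.** Cost-effectiveness is part of the hypothesis in section 1.1. Both arms are planned to receive the same two nerve blocks; only the combination arm adds 8 acupotomy sessions. A societal total cost should include care for complications of the procedures, whatever the reason recorded for the visit. The protocol itself recognises such risks: section 2.4.2 provides for hemostasis and for education on preventing infection, and section 2.5.2 excludes patients with earlier reactions to nerve block. Followed as written, the cost form would not capture a clinic or emergency visit for such an event.

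Sections 2.2 and 2.9.4 add to the gap. Injured patients are treated at the trial hospital and compensated through insurance. A patient asked about expenses may have paid nothing for that care, so it could go unreported even if it were in scope.

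A second, weaker point concerns utility. The trial collects an EQ-5D for the time of an adverse event within the economic evaluation, but the QALY rule does not say what is done with it.

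**Working it through.** **No figure to reproduce on this point.** The protocol gives no adverse-event rate, unit cost, utility or expected ratio. Its sample size reproduces: 20/(1 − 0.20) = 25 per group, 50 in total. That supplies the denominator below.

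**Which costs of a non-pain complication are counted?** Set against the list in 2.8.6:

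- Drugs for it: yes, as concomitant medication.
- Treatment materials, transport, patient time, productivity loss: not limited to radiculopathy, so they can be counted.
- Clinic, hospital or emergency care: no, because the only line for it is limited by reason for visit.

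**Effect on incremental cost.** Let S be the sum of uncounted facility costs in an arm.

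Missing incremental cost m = (S_combination − S_control)/25.

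One episode of cost C in one arm moves that arm's mean by C/25 = 0.04C; with 20 analysed per arm, by C/20 = 0.05C. If the arms have equal burdens, m = 0. If controls have more, m is negative.

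**Effect on the ratio, cost side only.** Let c = m divided by the planned incremental cost. Assuming positive incremental cost and positive incremental QALY, full ratio / planned ratio = 1 + c.

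| Assumed c | Full / planned |
|---|---|
| −1% | 0.99 |
| 0 | 1.00 |
| 1% | 1.01 |
| 5% | 1.05 |
| 10% | 1.10 |

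**Utility side, illustration only.** Assume an EQ-5D difference of 0.05 at weeks 2, 4 and 8 and none at baseline. By trapezoid the QALY gain is 0.05 × (1 + 2 + 4)/52 = 0.00673. If scheduled EQ-5D captures none of the loss, missed loss = excess event proportion × decrement × days/365, and the combined factor is (1 + c)/(1 − missed share).

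| Excess, decrement, days, c | Missed loss | Share of gain | Full / planned |
|---|---|---|---|
| 10%, 0.1, 3, 1% | 0.000082 | 1.2% | 1.01/0.988 = 1.02 |
| 20%, 0.2, 7, 5% | 0.000767 | 11.4% | 1.05/0.886 = 1.19 |
| 30%, 0.3, 10, 10% | 0.002466 | 36.6% | 1.10/0.634 = 1.74 |
| −10%, 0.1, 3, −1% | −0.000082 | −1.2% | 0.99/1.012 = 0.98 |

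**Is no capture realistic?** Post-baseline EQ-5D falls at visits 6, 11 and 12 of the combination arm. Six of the eight sessions (visits 2, 3, 5, 7, 8, 10) are on other days, but visits 5 and 10 come shortly before an assessment. In a trapezoid the week 2, 4 and 8 values stand for 14, 21 and 14 days. Assume a 5-day reaction equally likely after each session.

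- If EQ-5D is completed before that day's needling, reactions from visits 5 and 10 are caught. Expected captured time is (14 + 21)/8 = 4.4 days against a true 5, about 88%.
- If it is completed after needling, reactions from visits 5, 6, 10 and 11 are caught: (14 + 14 + 21 + 21)/8 = 8.75 days, an over-count.

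On average the scheduled EQ-5D may miss little, or may overstate the loss. The utility tables above are therefore not estimates of bias.

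**The case against.** The strongest case on the other side has five parts.

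1. **Harms are not left out altogether.** Medication, transport, patient time and productivity loss are counted without limit, and harm present at weeks 2, 4 and 8 is in the EQ-5D. Section 2.8.5 expects aggravated pain to be the main side effect, and a visit for that would plausibly count as a radiculopathy visit. This stands. The gap is facility care for non-pain complications.
2. **The QALY rule excludes nothing.** A reader might infer that the adverse-event EQ-5D is discarded. The rule does not say that only scheduled values are used. The recalled form is itself completed at visits and sits within the economic evaluation. Its role is unclear, not denied. This stands.
3. **Direction.** A reader might infer that the ratio must favour the more invasive arm. That needs excess events in that arm, and the documents give no rates. This stands.
4. **Sensitivity analyses are already planned** on all possible parameters, with a bootstrap. This helps on utility, but no sensitivity analysis recovers a cost that was never recorded.
5. **It is a condensed article and a preliminary study of 50 patients.** The cost line is not something left to a fuller document, however; it is a stated restriction. The small sample lowers the weight of the point but does not remove it.

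**Conclusion.** The cost point holds. As written, facility care for a non-pain complication of either procedure is outside total cost, which does not fit a societal perspective. (The sentence on perspective names direct nonhealthcare cost twice; I take one of these to mean healthcare cost, since 2.8.6 collects it.) If the combination arm has more such events, its incremental cost is understated by the excess facility cost per patient. There is no bias with equal burdens, and the sign reverses if controls have more. Neither size nor sign can be fixed from the documents; the factors from 0.99 to 1.10 above rest wholly on assumed cost shares.

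The utility point holds only as a request to reconcile the Table 1 footnote and 2.8.6 with section 2.9, part 4. A reader might compute, for example, that a reaction of 0.2 for 5 days (0.2 × 5/365 = 0.00274 QALY) cancels 36% of a gain of 0.05 × 56/365 = 0.00767, or 11% if 30% of patients are affected. Those figures are arithmetic on assumed values and suppose no capture by scheduled EQ-5D, so they should not be quoted as the size of a bias.

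**What to change.** **Main change, section 2.8.6.** Extend the facility-care item, in both arms, to visits made for radiculopathy or for any adverse reaction to a trial procedure. Include care provided at the trial hospital or paid by the insurer, taken from hospital or insurer records where the patient bears no charge. Causal relationship is already recorded under 2.8.5, so attribution needs no new assessment. The cost is one wording change on the case report form and retrieval of some billing data.

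**Secondary change, section 2.9, part 4.** State the role of the recalled adverse-event EQ-5D. One workable choice is a sensitivity analysis that applies the utility decrement only to event days not already reflected in the week 2, 4 or 8 EQ-5D, reporting the ratio with and without it. Subtracting the decrement over the whole event would double-count harm present at those assessments. The report should note recall error, and that the combination arm has 11 post-baseline visits at which to report a reaction against 5 in the control arm, so ascertainment is unequal. The cost is one extra analysis on data already planned; the ratio may move either way.
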